### Imaging data

Pseudo-anonymised longitudinal clinical imaging (MRI) for each patient will be collected and stored at a central imaging hub overseen by the Edinburgh Imaging Hub. Disease response assessment will be performed by practising UK neuroradiologists with a neuro-oncology interest via the Edinburgh Imaging Platform and additional analyses undertaken through the University of Edinburgh image analysis laboratory with permitted partners.

As per patient standard of care, it is expected that imaging will be performed preoperatively and postoperatively, for radiotherapy planning, following any chemoradiation, and as per follow-up determined by the managing MDT and/or if clinical concerns are raised regarding disease progression.

Pragmatic MRI protocols will be conducted as per SoC MRI protocols and timing following diagnosis and as such will be informed by the National Institute for health and Care Excellence guidelines from 2018,^30^ in line with the recent British Society of Neuroradiologists imaging guidance,^31^ which is itself an implementation of the Brain Tumour Imaging Protocol proposed by Ellingson.^32^ Where additional advanced imaging is performed, this is also encouraged to be submitted to the Edinburgh Imaging Hub and will be catalogued to permit any relevant subsequent analysis. Biopsy location imaging should also be submitted and standard operating protocols for the major neuro-navigation systems followed. Radiotherapy planning imaging will also be submitted.

The RANO assessments will be performed through a secure web portal provided by QMENTA Inc. There will be an ongoing 10% re-read to assess inter-rater agreement. It is anticipated that RANO reports will be provided within 2 weeks (10 working days) of successful transfer of imaging requiring assessment. RANO reports will categorise response where possible into complete response, partial response, stable disease or progressive disease. In cases of diagnostic uncertainty, potential or provisional outcomes may be recorded, allowing progression events to be backdated to the correct time point should subsequent imaging be confirmatory.

### Adverse events reporting

There are no study treatments within the TJBM study. Blood sampling and completion of QoL questionnaires are the only procedures that patients undergo additional to usual care. Therefore, it is not anticipated that there will be adverse events related to participation in this study. Only severe adverse events relating to those additional procedures will be reported as per Common Terminology Criteria for Adverse Events version 4^33^ and as defined in online supplemental appendix 7. The reporting period is from the date of informed consent to death.

10.1136/bmjopen-2022-067123.supp7Supplementary data

### Data management

Case report forms will be entered online via a secure web-based portal. Authorised staff at sites will require an individual secure login username and password to access this online data entry system. Paper CRFs will be available for backup only and must be completed, signed/dated and returned to the BRAIN MATRIX Study Office by the investigator or an authorised member of the site research team. Data reported on each CRF should be consistent with the source data or the discrepancies should be explained. If information is not known, this must be clearly indicated on the CRF. All missing and ambiguous data will be queried. All sections are to be completed.

All study records must be archived and securely retained for at least 25 years. No documents will be destroyed without prior approval from the sponsor, via the central Study Office. On-site monitoring will be carried out as required following a risk assessment and as documented in the Quality Management Plan. Any monitoring activities will be reported to the central BRAIN MATRIX Study Office and any issues noted will be followed up to resolution. BRAIN MATRIX will also be centrally monitored, which may trigger additional on-site monitoring. Further information regarding data management is provided in the study protocol.

The Cancer Research UK Clinical Trials Unit (CRCTU) will hold the final study dataset and will be responsible for the controlled sharing of anonymised data with the wider research community to maximise potential patient benefit while protecting the privacy and confidentiality of study participants. Data anonymised in compliance with the Information Commissioners Office requirements, using a procedure based on guidelines from the MRC Methodology Hubs, will be available for sharing with researchers outside of the trials team within 12 months of the primary publication.

### Trial organisation structure

The University of Birmingham will act as single sponsor to this multicentre study: Support Group, [name] (email: [contact]). The study is being conducted under the auspices of the CRCTU, University of Birmingham according to their local procedures.

The Chief Investigator, Co-investigators, Trial Management Team Leader, Senior Trial Coordinator, Trial Coordinator, Lead and Trial Statistician, Trial Monitor and patient representatives will form the SMG (current membership is listed in online supplemental appendix 1). The SMG will be responsible for the day-to-day conduct of the TJBM study, meeting at regular intervals (eg, at least every 3 months), or as required, usually by teleconference. They will be responsible for the set-up, promotion, ongoing management of the study, the interpretation of the results, and preparation and presentation of relevant publications.

Selected findings of clinical significance will be presented to the SAB, which as a minimum will include the Chief Investigator, an oncologist, a pathologist and a molecular biologist for a combined review of the molecular findings in context. The SAB may suggest amendments that will be incorporated into a SAB Report, which will be sent to the Executive Oversight Committee (EOC); current SAB and EOC membership is listed in online supplemental appendix 1. Possible re-testing/further testing may be required, as a result of SAB feedback. Guided decision-making tools that review results in the context of the literature and clinical experience will be piloted within the SAB. The SAB will also evaluate research and study proposals, manage data/tissue requests, and will report back to the EOC regarding any proposals or changes which they may suggest.

The overarching remit of the EOC is to mandate, including timeframe and deliverables, the responsibility of the SAB and to take responsibility of horizon scanning to enable the incorporation of new interventional arms. They will oversee the overall study management of both the platform and any standalone interventional trials. They will also liaise with other trial units and pharma stakeholders as well as funders, charities, study sponsors and policymakers and liaise with the BRIAN team. A quarterly EOC Report will be disseminated to all stakeholders that will demonstrate the performance metrics of each clinical site. In addition, the use of all samples given to external researchers via the SAB will be included in the report.

### Confidentiality

Confidential information collected during the study will be stored in accordance with the General Data Protection Regulation 2018. As specified in the PIS and with the patients’ consent, patients will be identified using only their date of birth and unique study ID number. Authorised staff may have access to the records for quality assurance and audit purposes. The BRAIN MATRIX Study Office maintains the confidentiality of all patients’ data and will not disclose information by which patients may be identified to any third party other than those directly involved in the treatment of the patient and organisations for which the patient has given explicit consent for data transfer (eg, laboratory staff).

### Trial status

Recruitment for the study opened in November 2020 and recruitment is expected to last for 5 years.

## Discussion

### Justification for patient population

The main aim of the TJBM study is to test the hypothesis that comprehensive genomic and epigenomic profiling of gliomas is feasible in a timely manner in the UK, and that the results improve stratification of patients for next-generation (targeted) therapies, ultimately improving outcomes and QoL.

Gliomas occur at all ages and their specific subtype is difficult to predict preoperatively. Therefore, the patient population eligible for the TJBM study is broad. It includes any patient who on preoperative assessment is suspected to have a diffuse glioma, or where a diffuse glioma remains a credible differential diagnosis, as established by the MDT at the recruiting site.

Recruitment is also open to patients with diffuse or atypical gliomas who had a biopsy before the launch of the TJBM study. This approach ensures that:

Patients with slow-growing diffuse gliomas that evolve over many years (oligodendrogliomas) may benefit from one or more of the clinical trials developed as part of the TJBM study and sample collection at tumour progression.Patients who potentially benefit most from comprehensive molecular diagnostics are not missed, which often are those with rare or atypical variants of glioma based on current diagnostics.^34^

The infrastructure for children with brain tumours in the UK is different to that of adults with epigenomic classification regularly used and with WGS shortly to be made available for all children with cancer. Thus, the challenges and opportunities are different for paediatric patients. Nevertheless, it is intended that children will be included within the TJBM study wherever appropriate. The recruitment of children and adolescents into the TJBM study will be coordinated with the UK’s paediatric oncology expert group(s).

### Justification for methodology

Neuroimaging with MRI plays a central role in the initial diagnosis and treatment stratification, surgical and radiotherapy planning, and assessment of disease response and progression in glioma.

Potential participants will have undergone MRI as part of a diagnostic work-up and an intracranial mass identified. As per current clinical practice, expert neuroradiological review will indicate glioma as the likely diagnosis, and a plan for treatment will be made by the relevant regional MDT meeting. Those with suspected glioma on MRI who are to undergo surgery and are otherwise eligible for the TJBM study will be approached. A proportion of these lesions that are subsequently diagnosed as types of brain tumours other than glioma will inevitably be included. They will not be included in the main analysis; however, data from these will be stored for additional research into those less common tumours which can be challenging to diagnose from imaging alone.

At the time of surgery, neuro-navigation will be used to capture the location of each biopsy taken for diagnosis and further molecular characterisation within the TJBM study. This will aid with subsequent analysis of tumour molecular markers and heterogeneity in the context of radio-genomics—a recent development in cancer imaging for assessment of disease in the personalised medicine era employing machine learning and artificial intelligence approaches.^32^

Early postoperative imaging for suspected HGG, including pre-contrast and post-contrast T1-weighted MRI, is currently recommended within 72 hours of surgery to minimise the presence of non-neoplastic enhancement. This imaging will be captured to permit eventual assessment of extent of resection, or the volume of residual enhancing disease, important prognostic factors for glioma. Subsequent to this, any additional imaging for radiotherapy planning, including CT, will be captured. Under the most recent response assessment in neuro-oncology^34^ recommendations for HGG from 2017, this is recommended as the baseline for assessing treatment response.^32^

All imaging will receive primary radiological reports at the local site as per current standard clinical practice. To deliver the imaging outcome requirements for clinical trials, centralised RANO reads will be delivered by a core group of UK Consultant neuroradiologists with a subspecialty interest in neuro-oncology imaging from TJBM study sites. Radiotherapy planning data in the form of dose distribution maps and associated data will be integrated into the imaging database to permit subsequent analysis of spatiotemporal response patterns of different glioma–treatment combinations in light of received radiation dose.

Local radiological reporting will inform clinical decision-making for individual patients. Central image analysis will provide resilient standardised assessment to meet internationally accepted standards which are suitable for peer-reviewed publication and are accepted by major regulatory approval bodies. All relevant preoperative and subsequent imaging will be identified for pseudonymisation and uploaded to the BRAIN MATRIX Imaging Platform in Edinburgh. This will be achieved through a dedicated online secure portal, with alternative secure online and physical transmission pathways available for redundancy. The accrued imaging data will form a core resource that will be leveraged for future imaging and clinical radiological research. The platform can also provide the basis for additional imaging studies within non-SoC imaging and advanced techniques, which would be separately funded and detailed in their respective project documentation.

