### Patient selection

Patients aged ≥16 years with newly diagnosed suspected WHO Grade II–IV glioma (as evidenced radiologically) suitable for a diagnostic or therapeutic surgical procedure resulting in a tumour sample matched to a blood sample or with progression with known WHO Grade II–IV glioma will be eligible.

Patients with primary spinal cord tumours, who are receiving active treatment of other malignancy, have contraindications to MRI and/or without standard of care imaging available, will be excluded.

Newly diagnosed patients with suspected WHO Grade II–IV glioma who are subsequently found to have a WHO Grade I tumour or non-brain tumour are expected to be a rare occurrence. If this event occurs:

If it is confirmed as a Grade I tumour, then the patient will remain eligible for the study and will continue to be followed up in accordance with the protocol.If it is confirmed as a non-brain tumour, then the patient will not remain on the study and no further follow-up data will be collected.

All patients must be able to provide written informed consent for the study.

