### Platform study outcome measures

The primary outcome measure of the platform is time from biopsy to integrated histological–molecular diagnosis (TTMD) defined as the difference (in days) between date of biopsy and date of WGS and epigenomic classification (EC).

Secondary outcome measures include those that are process centred, patient centred and framework based.

Process-centred secondaries include time to completion of each node of tissue and imaging pathway, tumour and biological sample(s) quality control (QC) status, imaging QC status and inter-rater agreement of response assessment in neuro-oncology (RANO).^26^

Patient-centred secondaries include extent of surgical resection, overall survival time (OS), intracranial progression-free survival time (PFS), QoL scores, type of interventions received, type of complications from treatments (standard of care) received, and concordance between initial local radiological diagnosis, local pathological diagnosis and integrated histological–molecular diagnosis.

Research framework–based secondaries include samples and images centrally stored, targetable mutation(s) identified, postmortem sampling consent status and sample collection confirmation, and number of applications to, and outputs resulting from, data repository (including trial proposals both within and outside of the TJBM network).

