OS is defined as the time from date of diagnosis to the date of death with patients who are alive at the time of analysis censored at the date last seen in clinic. Intracranial PFS time is defined as the time from date of registration to the earliest of date of intracranial progressive disease or death from disease. The date of an event is defined as the earliest confirmation of progression by radiological assessment, clinical symptoms or multidisciplinary team (MDT). Patients without progression at the time of analysis will be censored at the date last seen in clinic.

OS and intracranial PFS will be analysed and plotted using the Kaplan-Meier method. Median times with corresponding 95% CI will be reported together with rates at 1, 2 and 5 years. Multivariable survival regression modelling will be used to explore prognostic factors, including, but not limited to, WHO 2021 classification, age, tumour volume, stage, methylation and mutation status.

Longitudinal measures of QoL will be generated from the QoL questionnaire according to the questionnaire-specific algorithms for scoring. The analysis of longitudinal QoL scores will essentially be descriptive. For each of the multiple QoL scores generated from the different questionnaires, the means, medians or proportions (as appropriate) will be plotted over time together with 95% CI. These repeated measures over time may be modelled, if appropriate, with a linear or more flexible mixed model that takes account of the within-subject correlation and will allow exploration of factors associated with the outcome.

Details of the type of intervention received and complications (eg, surgical wound infection) relating to SoC treatments received will be monitored and recorded throughout the follow-up period and reported descriptively as frequencies and associated percentages. In relation to initial local logical diagnosis, local pathological diagnosis and integrated histological–molecular diagnosis, any difference between the tiers of diagnoses will be highlighted and categorised as discordant, agreed, refined and reported descriptively as frequencies and associated percentages.

Confirmation of central storage of images and material, relevant targetable mutations identified by WGS and EC, and receipt of postmortem consent forms with confirmed central storage of samples will be recorded and reported descriptively.

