The BRAIN MATRIX neuropathology and genomics team will generate an integrated report (histology, WGS, Heidelberg Classifier) for each case in consultation with the local neuropathology team. The primary BRAIN MATRIX report will comprise the formal routine GEL WGS report (germline and tumour) and Heidelberg Classifier report and integrate this with the histological and molecular report issued by the recruiting site. It is anticipated that a local histological and molecular diagnosis using immunohistochemical surrogate markers and targeted genetic analyses will be available before WGS and Illumina EPIC BeadChip data are returned to the Oxford BRAIN MATRIX Laboratory. When available, the BRAIN MATRIX neuropathology and molecular genetics team will conduct a virtual MDT meeting with the referring site to ensure all relevant information will be incorporated in the final BRAIN MATRIX diagnostic report. Variant calling and classifier outputs will be determined by the practice at the GEL/Illumina Centre and the version of the Heidelberg Classifier algorithm active at the time of sample analysis.

Where relevant germline data are identified, local sites should facilitate local genetic referral as per other GEL study protocols.

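### If tumours that prove not to be glioma are left out of the diagnostic-concordance analysis, glioma/non-glioma discordance is removed by construction and agreement is overstated

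*Protocol article*

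**What the plan says.** Platform study outcome measures lists among the patient-centred secondary outcomes "concordance between initial local radiological diagnosis, local pathological diagnosis and integrated histological–molecular diagnosis". The Statistical analysis plan section says of this outcome that "any difference between the tiers of diagnoses will be highlighted and categorised as discordant, agreed, refined and reported descriptively", as frequencies and percentages. Neither section names a denominator or analysis set.

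Three rules decide what happens when a suspected Grade II–IV glioma turns out to be something else:

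- **Grade I tumour** (Patient selection): "the patient will remain eligible for the study and will continue to be followed up in accordance with the protocol".
- **Non-brain tumour** (Patient selection): "If it is confirmed as a non-brain tumour, then the patient will not remain on the study and no further follow-up data will be collected".
- **Other brain tumour** (Discussion, Justification for methodology): "A proportion of these lesions that are subsequently diagnosed as types of brain tumours other than glioma will inevitably be included". Of these patients the article then says: "They will not be included in the main analysis; however, data from these will be stored for additional research".

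The term main analysis is not defined. Patient selection expects Grade I and non-brain tumours to be rare and has no rule for other brain tumours. No figure is given for any of the three groups.

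**The concern.** Newly diagnosed patients are registered because imaging suggests glioma. A patient whose tissue shows another tumour is the plainest case of imaging and tissue disagreeing. The exclusion is triggered by the later diagnosis, which is itself one of the tiers being compared. A concordance percentage computed on the remaining patients is therefore conditioned on its own result.

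What is at stake is the figure that tells readers how often the preoperative imaging diagnosis holds up. It would look better than it is, by an amount that cannot be judged from the published percentage. The pathology tier could be touched too, because the article does not say whether the local or the integrated diagnosis decides that a tumour is not a glioma. The main effect is on radiology.

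**Working it through.** The article states no expected concordance, no non-glioma share and no statistical basis for its sample size, so it has no figure to reproduce. The check is a reading of the rules followed by an illustration.

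**Step 1: the selection.** Entry depends on radiological suspicion (Patient selection), or on glioma being a credible differential (Justification for patient population). Exclusion depends on the later diagnosis. In the radiology-by-final-diagnosis table for newly diagnosed patients, the cell for suspected glioma with another brain tumour as final diagnosis is therefore empty in the main analysis set, whatever its true frequency. Cells for a different glioma subtype, grade or molecular status remain filled, as do cells for reclassification to Grade I glioma.

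**Step 2: inputs.**

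- N = 1000, the target sample size (Statistical analysis plan section).
- q, the share of analysed patients who prove not to have glioma: not given; assumed 1% to 10%.
- d, discordance among retained patients: not given; assumed 10%, with 5% and 20% as a range. The 10% is loosely anchored to the statement in Justification for molecular diagnostics that the classifier alters diagnoses and grades in more than 10% of biopsies.
- Every non-glioma is counted as discordant (assumption).

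**Step 3: formulas.**

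- Discordance in all patients = q + (1 − q)d
- Discordance after exclusion = d
- Understatement = q(1 − d)
- Share of discordant cases lost = q / [q + (1 − q)d]

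**Step 4: results with d = 10%.**

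| q | Non-glioma | Discordant among retained | All patients | After exclusion | Difference (points) | Discordant cases lost |
|---|---|---|---|---|---|---|
| 1% | 10 | 99 of 990 | 109/1000 = 10.9% | 10.0% | 0.9 | 10/109 = 9% |
| 2% | 20 | 98 of 980 | 118/1000 = 11.8% | 10.0% | 1.8 | 20/118 = 17% |
| 5% | 50 | 95 of 950 | 145/1000 = 14.5% | 10.0% | 4.5 | 50/145 = 34% |
| 10% | 100 | 90 of 900 | 190/1000 = 19.0% | 10.0% | 9.0 | 100/190 = 53% |

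**Step 5: against sampling error.** At q = 5% the Wilson 95% interval is 12.45% to 16.82% with all patients and 8.25% to 12.07% after exclusion, so the reported interval would miss the true 14.5%. At q = 1% the intervals are 9.12% to 12.98% and 8.28% to 12.03%, and the 0.9-point difference is smaller than the half-width of about 1.9 points, (12.03 − 8.28)/2.

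**Step 6: sensitivity.** With d = 5% the understatement runs from 0.95 to 9.5 points; with d = 20%, from 0.8 to 8.0 points. Between 45 and 198 discordant patients stay visible over these ranges, never zero. If only a fraction f of the non-gliomas contradicts the recorded radiological diagnosis, the understatement becomes q(f − d). That is smaller, and positive as long as f exceeds d.

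**The case against.** The strongest reply is that the exclusion is not shown to reach this outcome. It stands in a Discussion rationale, refers to an undefined main analysis, and keeps the data. Concordance is a secondary, descriptive outcome, and a fuller protocol or analysis plan may define its own set. For non-brain tumours only further follow-up stops; diagnoses already recorded are not said to be deleted. This stands in part: the point is conditional. But the article does state an exclusion rule and names no other set for concordance, so someone following the text would apply it.

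The size is also open to challenge. Patients may enter when glioma is only one credible differential, so a non-glioma result need not contradict the recorded imaging diagnosis. Patients who enter at progression of a known glioma will dilute q. Both points stand, and are why the figures are shown as a range.

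Three stronger readings are tempting, and the article does not support them:

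- **That the outcome cannot show discordance at all.** Differences within glioma and Grade I reclassification remain countable.
- **That comparing local pathology with the integrated diagnosis is circular**, because the central report is to "integrate this with the histological and molecular report issued by the recruiting site". Combining histology with molecular data is how the integrated diagnosis is defined. The sequencing and classifier outputs are determined outside the local site and can overturn the local diagnosis. No inflation can be quantified from the article.
- **That Patient selection and Justification for methodology contradict each other**, one calling such cases rare and the other inevitable. They describe different groups; the defect is that the former has no rule for other brain tumours.

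**Conclusion.** The point holds in conditional form and is of moderate weight. If the main analysis set is used for concordance, glioma/non-glioma discordance is removed by construction and agreement is overstated, chiefly for radiology. With 10% discordance among retained patients and a non-glioma share of 1% to 10%, all counted as discordant, true discordance of about 11% to 19% would be reported as 10%. At the low end the bias lies within sampling error; from about 5% it does not. The non-glioma share is an assumption throughout.

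A reader might also infer that the primary outcome (time to integrated diagnosis) and the sample QC proportions are distorted in the same way. The article does not say so: QC is reported per type of sample with no restriction by diagnosis, and nothing states how failed work-ups are handled. These outcomes need a clarifying sentence; no error is shown. Nor does it follow that the added value of sequencing and epigenomic classification is understated, since local histology alone may identify many of the non-gliomas.

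**What to change.** 1. State that diagnostic concordance is analysed in all registered patients with a tissue diagnosis, whatever the final diagnosis, including diagnoses already recorded for patients who leave the study with a non-brain tumour.
2. State that the process outcomes (time to integrated diagnosis, sample QC) are likewise not restricted by the resulting diagnosis.
3. Restrict to confirmed glioma only for OS, PFS and the prognostic models.
4. Align Patient selection with Justification for methodology, so that one rule covers Grade I, non-glioma brain and non-brain tumours, for both follow-up and analysis. It should also place a Grade I tumour that is not a glioma, which as worded falls under two rules.
5. Use the local pathological diagnosis as recorded before the sequencing and epigenomic results return. Sample analyses already expects it to be available by then.

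The cost is wording. Data on the other brain tumours are already to be stored, and no new data collection is needed. The downside is that reported concordance will be less favourable.
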